**Sample size and power analysis**

Sample calculation was performed using the G * Power software, based on the measure of the level of pain, as it is the primary outcome of the research. A power of 0.80, error probability α 0.05, effect size of 0.5 and dropout rate of 15% were used, for this we will recruit 60 participants (30 in each group)^9^.

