**Outcome assessment**

**Primary outcome**

There is one primary outcome measure: 1) Average pain in the previous week.

1) Pain intensity will be assessed at baseline and after treatment in 8 weeks. They will also be evaluated at 60 weeks, which is a secondary time point for the primary outcome. Pain intensity will be assessed using the visual analogue scale (VAS)^5^. Formed by a 100 mm horizontal line, anchored by the words “no pain/discomfort” and “worst imaginable pain/discomfort”^5^. To measure pain, the participant will be asked to indicate the level of pain they are currently feeling and the average pain they felt in the last week, marking the scale with a line. A ruler will be used to measure the obtained value^5^.

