**Statistical analysis**

The study will be run as a superiority trial. The statistical analysis will follow the intention-to-treat concept. Statistical analysis will be performed using the software IBM SPSS Statistics for Windows, version 20.0 (IBM Corp., Armonk, N.Y., USA) and statistician will be blind. Data will be evaluated using exploratory statistical techniques. Firstly, the normality and homogeneity of the data will be verified and then the appropriate statistical analyses will be adopted for the variables. The between-group differences and their respective confidence intervals at 95% will be calculated by constructing mixed linear models interaction of group data versus time. The linear mixed-effect model will be applied to the primary and secondary outcomes. “Time” and “group” will be considered fixed effects, whereas the participants will be considered random effect. The dependent variable baseline values will be included as a covariate for the correction of possible baseline between-group differences.

A causal mediation analysis will be conducted using the “mediate” package in R (The R Foundation for Statistical Computing). A model-based inference approach will be used to estimate the average causal mediation effect (ACME), average direct effect (ADE) and the average total effect^29^.

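### If the mixed model is fitted as worded, with a plain participant random intercept, the standard error of the primary week-8 pain difference is built from week-8 and week-60 variances averaged together

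*Protocol*

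**What the plan says.** The Primary outcome section sets the time points for average pain on the 100 mm scale: "Pain intensity will be assessed at baseline and after treatment in 8 weeks", followed by "They will also be evaluated at 60 weeks, which is a secondary time point for the primary outcome". Week 8 therefore carries the primary comparison, and week 60 is a later reading of the same variable.

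The Statistical analysis section states the model. Group differences and their 95% intervals are to be "calculated by constructing mixed linear models interaction of group data versus time". Time and group are fixed effects, "whereas the participants will be considered random effect". It adds: "The dependent variable baseline values will be included as a covariate". No other random term and no residual covariance structure is named.

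Before the model is described, the same section says that "the normality and homogeneity of the data will be verified and then the appropriate statistical analyses will be adopted". It gives no rule for what follows if a check fails, and does not say whether homogeneity is meant between groups, between visits or both.

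**The concern.** A mixed model whose only random term is a participant intercept, with independent residuals of equal variance, implies compound symmetry: one common outcome variance at every visit. Because baseline is a covariate, the natural repeated outcomes for pain are weeks 8 and 60. Week 8 closes an 8-week programme of 16 supervised sessions. Week 60 comes a year later, with no protocol treatment described in between. Nothing in the protocol supports equal spread at two such different times.

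At stake is the precision claimed for the primary result. Under that fit, the width of the week-8 interval depends partly on how variable pain is at a secondary time point. If week 60 is less variable, the week-8 interval is too narrow and the test rejects too often. If week 60 is more variable, the interval is too wide and power is lost.

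**Working it through.** **Inputs from the protocol.** The sample is 30 women per group. The sample-size section states: "A power of 0.80, error probability α 0.05, effect size of 0.5 and dropout rate of 15% were used". After 15% dropout, 30 × 0.85 = 25.5 women per group remain. The protocol gives no pain SD at either visit, so it contains no figure on this point to reproduce.

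**Assumptions.** The outcomes in the model are exactly weeks 8 and 60, and the fit is a plain random intercept with one residual variance. Let s8 and s60 be the baseline-adjusted SDs and r = s60/s8. The value of r is unknown and is shown as a range.

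**Formula.** With complete data the model estimates one total variance, (s8² + s60²)/2, and uses it at week 8 in place of s8². Hence:
- SE ratio (model-based over true) = √((1 + r²)/2)
- coverage = 2Φ(1.96 × SE ratio) − 1
- two-sided type I error = 1 − coverage

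**Two examples.**
- r = 0.8 (for instance 25 mm at week 8, 20 mm at week 60): √((1 + 0.64)/2) = √0.82 = 0.906, so the SE is 9% too small. 1.96 × 0.906 = 1.775. Type I error is 7.6% and coverage 92.4%.
- r = 1.25 (for instance 20 mm and 25 mm): √((1 + 1.5625)/2) = √1.28125 = 1.132, so the SE is 13% too large. 1.96 × 1.132 = 2.219. Type I error is 2.7% and coverage about 97.4% (2.65% and 97.35% before rounding).

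**Range.**

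| r = SD60/SD8 | SE ratio | Coverage of nominal 95% CI |
|---|---|---|
| 0.5 | 0.791 | 87.9% |
| 0.67 | 0.851 | 90.5% |
| 0.8 | 0.906 | 92.4% |
| 0.9 | 0.951 | 93.8% |
| 1.0 | 1.000 | 95.0% |
| 1.1 | 1.051 | 96.1% |
| 1.25 | 1.132 | 97.4% |
| 1.5 | 1.275 | 98.8% |
| 2.0 | 1.581 | 99.8% |

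**Power when the SE is too large.** Take the stated effect size of 0.5 as a difference in units of s8 (the protocol does not say which kind of effect size it is), with 25.5 women per group. The noncentrality is 0.5/√(2/25.5) = 1.785. With the correct SE, power is Φ(1.785 − 1.96) = 43%. At r = 1.25 it is Φ(1.785 − 2.219) = 33%. These figures serve only to compare the two analyses. Whether 60 women are enough is a separate question.

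**Simulation check.** The random-intercept model was fitted by REML with 30 women per arm, within-person correlation 0.5 and 4000 runs per setting.

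| r | Coverage, complete data | Coverage, 15% missing at week 60 |
|---|---|---|
| 0.5 | 87.7% | 88.2% |
| 0.8 | 92.9% | 92.8% |
| 1.0 | 94.5% | 95.0% |
| 1.25 | 97.4% | 97.2% |
| 2.0 | 99.8% | 99.5% |

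The simulation agrees with the formula. A week-8-only ANCOVA on the same data held coverage between 94.4% and 95.5% at every ratio, so the error comes from pooling the variances and disappears when week 8 uses its own.

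**The case against.** The strongest reply is that the text does not commit to this fit. A reader might infer that the protocol forces equal variance and that the participant effect is the sole covariance term. It says neither. A participant random effect is compatible with visit-specific residual variances, the levels of time are not listed, and residual covariance is often settled in a statistical analysis plan, which is not at hand. This stands as a limit on the claim, and the point is therefore conditional. It does not remove the point: the protocol goes beyond announcing a mixed model and names the random term, and fitting what is named gives compound symmetry.

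A second reply is that homogeneity will be checked first. The check has no decision rule and does not mention visits, and any remedy would be chosen after seeing the data. That is weak protection for a primary analysis.

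A third reply is that every size shown rests on assumed SDs. That is correct. A reader might infer that the primary test is anti-conservative, or that the interval is materially wrong whenever the spreads differ. The protocol supports neither inference: it gives no ground for expecting week 60 to be the less variable visit, and at ratios of 0.9 to 1.1 the departure from 95% is about one percentage point.

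It might also be argued that a single baseline slope for both visits adds to the error, because baseline should predict week 8 better than week 60. The protocol offers no support for that. Under randomisation a common slope affects precision and does not bias the group contrast.

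**Conclusion.** The concern holds in conditional form. Fitted as worded, with a plain random intercept and one residual variance over weeks 8 and 60, the model bases the primary week-8 standard error on the average of two visit variances. The consequence is minor when the SDs are within about 10% of each other. It becomes relevant at a ratio of about 0.8 or below (type I error 7.6% or more) or about 1.25 or above (type I error 2.7% or less, with power in the example falling from 43% to 33%). Neither the direction nor the size can be settled from the protocol. With complete data the point estimate is not biased; what is affected is its standard error, interval and test. The figures assume a joint model containing exactly these two visits. Because the direction is unknown and the remedy is cheap, the wording should be changed.

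**What to change.** In the Statistical analysis section, for outcomes measured at both week 8 and week 60, replace the plain participant random intercept by a repeated-measures mixed model with an unstructured covariance over the two visits, and state that the primary week-8 difference is estimated from it. The named software can do this through the repeated-measures specification of its mixed-model procedure. Alternatively, state that the primary contrast is a week-8 ANCOVA adjusted for baseline, and keep the two-visit model for week 60. A baseline-by-visit term is optional and bears on precision only.

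The unstructured model has three covariance parameters instead of two, which about 51 women (60 × 0.85) can support. If the two spreads prove equal, almost nothing is lost. No new data or visits and no change to the sample size are needed.

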2) Isometric strength of the hip abductor and extensor muscles will be assessed at baseline and after treatment, 8 weeks during post-intervention reassessment. A manual dynamometer model Lafayette (Lafayette Instruments) will be used, which has proven to be a valid method for evaluating isolated muscle contraction strength^22^. To assess the hip abductor musculature, participants will be placed in the supine position on a stretcher, stabilized by velcro bands around the pelvis and above the lateral ankle malleolus to avoid compensatory movements and the influence of the assessor resistance^22^. The dynamometer will be positioned above the lateral ankle malleolus and fixed to the stretcher by an inelastic strap, it will be positioned without rotation, with 10º of hip abduction to minimize the potential for compression of the tendons against the greater trochanter^14^. The untested lower limb will be positioned with 45º of hip and knee flexion, with the foot positioned on the stretcher and the upper limbs supported by the side of the body (figure 2)^14^. For evaluation of the hip extensors, participants will be positioned in the prone position with knee flexion on the lower limb to be evaluated. The dynamometer will be positioned on the posterior region of the thigh, above the popliteal fossa and will be stabilized by an inelastic velcro strap^23^. Another Velcro strap will be placed around the pelvis (figure 3)^23^. The measurement of limb length will be performed with a measuring tape to calculate torque, from the greater trochanter to the center of the dynamometer, and will be recorded in meters^23,24^. The maximum voluntary contraction tests will be performed 3 times with 5 seconds of duration for each contraction, with 30 seconds of rest between each attempt^23^. Participants will be verbally encouraged to perform as much strength as possible during the test. The strength values ​​will be normalized by the weight of each participant^23^.

Figure 2. Assessment of isometric strength of hip abductor muscles

[figure not shown]

Figure 3. Evaluation of isometric strength of hip extensors muscles

[figure not shown]

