6) Muscle recruitment during treadmill walking (MOVEMENT^®^) will be assessed at baseline and after treatment at 8 weeks follow-up. Surface electromyography will be used in three different walking conditions: preferential speed, top speed but no running and 3.0km/h. Each speed will be recorded for one minute. The familiarization with the treadmill will be carried out for 5 minutes at the self-selected speed, the interval between each test of each speed will be 1 minute and the participants will take the test barefoot^13^. The electromyographic signals will be captured using an 8-channel biological signal acquisition model module (New Miotool Wireless, Porto Alegre, Brazil) with 2000 gain, 16-bit A/D converter, 1010 Ohm / 2 pF input impedance , common mode rejection ratio 126 dB, bandpass filter 20–500 Hz and sampling rate 2 kHz. In addition, the software allows real-time filming via the webcam. All wires will be joined and secured to avoid motion artifact. The muscles of each participant will be located, according to the SENIAM group, and the electrodes will be placed unilaterally on the affected side (or more painful if bilateral) and longitudinally oriented with the muscle fibers of the muscle to be evaluated^10,13^. Trichotomy will be performed in the area of ​​electrode placement and skin abrasion with gauze to reduce impedance, in addition to the use of alcohol to clean the skin^13,14,15^. Active bipolar electrodes will be used, which will be placed in a bipolar configuration, with a capture area of ​​1cm in diameter and a distance of 2cm between them^13,14^. A reference electrode will be placed over the ulnar styloid process. The muscles evaluated are:

- Gluteus medius (GMED): electrodes will be placed 50% along a line from the iliac crest to the most lateral point of the greater trochanter.
- Gluteus maximus (GMAX): The electrodes will be placed 50% along a line between the sacral vertebrae and the most lateral point of the greater trochanter. This position corresponds to the greatest prominence of the middle of the buttocks, well above the visible bulge of the greater trochanter.
- Tensor fascia latae (TFL): The electrodes will be placed proximally 1/6 of the way along a line from the anterosuperior iliac spine (ASIS) to the lateral femoral condyle.

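### For week-8 pain, every listed candidate mediator is read at the same visit as the outcome, so the planned mediation analysis cannot support a causal claim there

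*Protocol*

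**What the plan says.** The Statistical analysis section of the protocol states: "A causal mediation analysis will be conducted using the “mediate” package in R". It will estimate the "average causal mediation effect (ACME), average direct effect (ADE) and the average total effect" by a model-based approach. Mediator, mediation outcome, visit and covariates are not given.

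The visit schedule is fixed in the Outcome assessment section:

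- Pain (Primary outcome): "Pain intensity will be assessed at baseline and after treatment in 8 weeks". For later follow-up: "They will also be evaluated at 60 weeks, which is a secondary time point for the primary outcome". The recall window is stated as well: "There is one primary outcome measure: 1) Average pain in the previous week".
- Strength (Secondary outcomes, item 2): "Isometric strength of the hip abductor and extensor muscles will be assessed at baseline and after treatment, 8 weeks during post-intervention reassessment".
- EMG recruitment (item 6): "will be assessed at baseline and after treatment at 8 weeks follow-up".
- Catastrophizing, kinesiophobia and central sensitization (items 3 to 5): baseline, week 8 and week 60.

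The Interventions section also describes a weekly load progression test scored on the modified Borg scale in both arms. It is not listed as an outcome or as a mediator.

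**The concern.** A causal mediation estimate needs the mediator to act on the outcome and not the other way round. Randomisation protects the path from arm to mediator and from arm to pain. It does not protect the path from mediator to pain, which rests on time order and on control of common causes. When mediator and pain are read together, the data cannot tell a mediator that relieved pain from pain relief that changed the mediator.

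The second direction is plausible here. Catastrophizing and kinesiophobia concern the response to pain, and maximal contractions are tested in a painful hip.

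The Introduction and Discussion argue for motor control training partly on mechanism. A non-zero indirect effect could therefore be taken as support for that mechanism when none was shown. What is at stake is this secondary causal claim, not the comparison of the arms.

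**Working it through.** **Plan's own figure.** The protocol gives no figure for the mediation analysis, so there is none to reproduce.

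**Step 1: schedule.** Readings after randomisation, from the Outcome assessment section:

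| Measure | Between baseline and week 8 | Week 8 | Week 60 |
|---|---|---|---|
| Pain (VAS) | none | yes (primary) | yes (secondary) |
| Strength | none | yes | no |
| EMG recruitment | none | yes | no |
| Catastrophizing | none | yes | yes |
| Kinesiophobia | none | yes | yes |
| Central sensitization | none | yes | yes |

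None of the five candidate mediators has a reading after baseline and before week 8. Week-8 pain refers to the preceding week, so its window runs from about week 7 to week 8 and opens before the mediator is read.

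**Step 2: size of the false share.** Take the extreme case in which the mediator has no effect on pain.

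- Pain at week 8: P8 = τ·arm + error, within-arm variance 1.
- Mediator: S = −ρ·P8 + error, within-arm variance 1, where ρ is the within-arm correlation in absolute value.
- Arm effect on mediator: −ρτ. Coefficient of S in the pain model given arm: −ρ.
- Estimated ACME = (−ρτ)(−ρ) = ρ²τ. Total effect = τ. Share = ρ². The true share is 0.

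The values of ρ are assumed, since the protocol gives none: 0.3² = 9%, 0.5² = 25%, 0.7² = 49%.

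Adjusting both models for baseline pain, with an assumed correlation of 0.5 between baseline and week-8 pain, gives a share of 0.75ρ²/(1 − 0.25ρ²):

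- ρ = 0.3: 0.0675/0.9775 = 7%
- ρ = 0.5: 0.1875/0.9375 = 20%
- ρ = 0.7: 0.3675/0.8775 = 42%

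**Step 3: how often it would look significant.** Inputs from Sample size and power analysis are an effect size of 0.5 (taken here as a standardised mean difference), 60 participants and 15% dropout, so 60 × 0.85 = 51 completers. The model of Step 2, without baseline adjustment, was simulated with 2,000 trials per setting (200 at N = 2,000). The table gives the share of trials in which the 95% interval for the ACME excludes zero.

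| ρ (assumed) | N = 51 | N = 60 | N = 2,000 |
|---|---|---|---|
| 0 | 0.3% | 0.2% | 0% |
| 0.3 | 5% | 5% | 94% |
| 0.5 | 15% | 17% | 100% |
| 0.7 | 25% | 30% | 100% |

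The N = 2,000 column shows that this is bias and not small-sample noise. With an assumed larger arm effect of 0.8, the N = 51 figures rise to 8%, 30% and 51%.

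**Step 4: does moving to week-60 pain cure it?** Let week-8 pain persist with no mediator effect: P60 = φ·P8 + error.

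- Coefficient of S in the week-60 pain model given arm: −ρφ.
- ACME = (−ρτ)(−ρφ) = φρ²τ. Total = φτ. Share = ρ², the same as before.
- Baseline pain adjustment trims it to the same 7%, 20% and 42%.
- With week-8 pain in the models, S carries no further information on P60. Its coefficient is 0 and the false share is 0%.

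The lag alone therefore does not help, because week-8 pain is a common cause of the week-8 mediator and week-60 pain.

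**The case against.** The strongest reply is that the protocol never commits the mediation analysis to week-8 pain or to any mediator, that these choices are normally left to an SAP, and that week-8 mediators with week-60 pain fit the text as written. The first part stands: a reader might infer that strength or recruitment is to be tested as the mediator of week-8 pain, but the protocol does not say so, and the silence is not the fault raised here. What remains is that the protocol fixes the visits. An SAP can name a mediator, but it cannot create a reading of a listed outcome before week-8 pain.

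Four stronger readings are also unsupported.

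- Nothing is recorded during treatment. This is not so: the load test is weekly in both arms. It is simply not defined as an outcome, and progression may itself be held back by pain.
- The model would appear to confirm the mechanism. At the protocol's effect size and about 51 to 60 participants, a falsely significant ACME is a minority result even under pure reverse causation, which is the worst case.
- The strength test position shows that pain drives strength. The position is chosen to reduce tendon compression, which would if anything weaken the influence of pain on that test.
- Drop-out will be larger at week 60. The protocol gives a single 15% and no figure by visit.

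**Conclusion.** The point holds for week-8 pain: no listed outcome supplies a mediator reading that precedes it, so an ACME or ADE at that visit cannot carry a causal meaning. Under pure reverse causation the false share is ρ² (9% to 49% over the assumed range of 0.3 to 0.7), or about 7% to 42% after baseline pain adjustment. These sizes rest on linear models, no true mediation and assumed correlations. If some true mediation exists, the estimate mixes the two and the data cannot separate them.

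A reader might infer that using week-60 pain repairs the analysis. Step 4 shows that it does not unless week-8 pain is also handled. The randomised comparison of pain between arms is untouched.

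**What to change.** In the Statistical analysis section:

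1. State that any model pairing a week-8 mediator with week-8 pain is reported as an association only, with no causal or mediation claim.
2. If a lagged model is used (week-8 mediator, week-60 pain), account for week-8 pain as well as baseline pain and the baseline mediator. State that the estimate then excludes mediation already completed by week 8, and that week-8 pain is itself affected by treatment, so the result is not the full mediated effect.
3. Report a sensitivity analysis for unmeasured mediator-outcome confounding with any lagged result.

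The cost is wording and some extra analysis; no new visits or data are needed. The price is a weaker mechanistic claim, and any lagged result sits at the secondary time point.

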**DISCUSSION**

This study aims to assess whether there will be a difference in hip pain intensity between individuals with GTPS who underwent an exercise protocol with emphasis on motor control training and those who underwent a nonspecific general exercise program. Considering that no study used neuromuscular training as a treatment strategy for GTPS and there is insufficient evidence on the influence of this intervention on clinical and biomechanical aspects, this study is necessary. The study will use two different protocols that are easy to clinically apply, with simple and well-described exercises, accessible equipment, so that participants can adopt these self-management programs.

Exercises are considered the cornerstone nonsurgical treatment for chronic musculoskeletal pain^17^. We chose two types of protocols: the MCG was developed to be specific to the target muscle group, focusing not only on strengthening but also on improving gait patterns, maintaining correct and efficient movement patterns, and providing guidance on how to avoid aggravating positions as excessive adduction of the femur during functional activities. For the GEG, a general and non-specific exercise protocol will be applied, without guidance on positioning or strategies to avoid worsening pain - only non-specific warm-up, stretching and strengthening exercises will be performed. These different approaches will be compared to determine any differences in our primary hip pain outcome measures, and whether there is any effect on the secondary physical and psychological outcome measures.

GTPS is, by definition, a painful syndrome, therefore, the specific cause of pain may be difficult to define, as more than one pathology can present similar symptoms in the hip region^5,6,17,19^. We will apply a combination of multiple clinical tests to avoid including participants who do not have GTPS, eg hip osteoarthritis^17,19^. The diagnosis of GTPS is clinical and two studies by Grimaldi et al. 2017 and Ganderton et al. 2017 demonstrated that palpation over the greater trochanter has a sensitivity of 80% and 85.7%, respectively, and a specificity of 47% and 61.1%, respectively. They also reported likelihood ratios of 0.43 and 2.2, respectively, demonstrating that this test alone, when negative, is able to rule out the presence of GTPS^6,19^. However, the combination of palpation and one of the other tests, FABER, Single leg stance for 30 seconds , FADER, FADER-R, ADD, ADD-R increases the chances of detecting GTPS due to the specificity of these tests, which can reach 100%^19^.

In order to maintain methodological quality, this clinical trial will comply with the standards of the consort group^30^. Study participants will be randomized to join one of the groups through the concealed allocation^17.30^. Due to the nature of the intervention, it is not possible to blind the clinician or participant to group allocation. Only the assessor of outcome measures and the statistician are able to be blinded to treatment allocation. The importance of not revealing anything to the assessor about the nature of the treatment will be strongly emphasized to participants. Statistical analysis will be conducted blind to treatment group allocation - actual groups will only be revealed after analysis. In addition, intention-to-treat analysis will be used, which preserves the study's randomization and simulates the real-life situation^31^. As a limitation of the study, we highlight the participation of women only, so care must be taken when extrapolating data to men with the same conditions.

The research idea came from studies that indicated physical exercise as the first line of treatment for the management of tendinopathies in the upper and lower limbs, such as the GTPS^5,12,17^. General exercise has the ability to decrease nociceptive afferent input to the central nervous system and thus decrease pain^10^, however, our motor control protocol consists, in addition to isotonic exercises, of isometric exercises that have been reported as important for the improvement of the peripheral and central pain, cortical inhibition releasing and reducing pain in the tendon^32^. In addition, the MCG consists of neuromuscular training, with correction and maintenance of the dynamic alignment of the lower limbs during gait training, which may be the reason why this protocol is superior to GEG. The findings of this study will contribute to determine the effect on hip pain of both MCG and GEG in the treatment of individuals with GTPS. This information can be used by health professionals to assist them in clinical decision making and in selecting the most appropriate training program for the management of GTPS.

